### Data collection and management

The data from all measurements will be recorded on paper by the blinded outcome assessors. Patients are instructed not to inform the assessor about group allocation.

The outcome assessors are physical therapists of the MUMC^+^. The performance measures and strength assessments are part of their routine tasks and no special training prior to the study was needed. The purpose and scoring method of all questionnaires used was explained by the programme coordinator prior to the start of the study. Furthermore, the outcome assessors practised data collection several times in order to get an idea of the time needed. The data are recorded on paper, with numbers used to represent the rank order within the recruitment process in order to guarantee that the data is analysed separately from personal data. The data in these paper case reports are digitised by research assistants and the programme coordinator will enforce data integrity through range checks and cross-validation between the same variables assessed on repeated occasions. In addition, visual record verification will be done by comparing the first ten records of a data set with the corresponding paper case reports [91]. If no inconsistency is found, the programme coordinator will check every tenth record until an incorrect record is found. After correction of the incorrect record, all following records will be checked until successive records free of inconsistencies are found [92]. All data on paper will be stored in a locked archive for a maximum of 15 years. Only the programme coordinator has access to personal data. After the analysis, other researchers of the team ([name]) will also have access to anonymous data.

### Sample size

The present study is the first to evaluate the effects of aqua-cycling in patients with mild to moderate knee OA. There are no previous data on which to base the sample size calculation. The estimation of the sample size is based on two factors: [1] the minimum clinically important difference (MCID) of WOMAC, and [2] studies with a similar design (aquatic therapy versus usual care) or intervention (one group pre-test/post-test feasibility study of aqua-cycling for rheumatic patients). Although the present study uses the KOOS questionnaire, the WOMAC questionnaire has been used to estimate the sample size. The WOMAC is well recognized in OA research and the questionnaire and minimum clinically important differences (MCID) of the WOMAC subscales are known. The MCID changes from baseline to post-interventions on the WOMAC pain and function scale range from 15 % to 18 % for pain and 12 % to 17 % for physical function [75, 93]. The results of previous studies are in line with or exceed the MCIDs referred to. Hinman et al. showed a 21 % and 29 % improvement in WOMAC pain and function scores for the hydrotherapy group [36]. The usual care group did not improve. A feasibility study of an aqua-cycling programme for rheumatic patients showed an improvement of 14 % in the post-intervention score of self-reported physical functioning [23]. Based on the above mentioned data, the aqua-cycling training in the present study is expected to achieve at least similar results as the interventions of Moser and Hinman, or even exceed those results because of a higher exercise frequency and intensity and longer duration of the intervention [23, 36]. Thus, a difference of 25 % between the aqua-cycling group and usual care group in terms of reduction of knee pain and improvement in physical functioning is hypothesised as clinically meaningful. The statistical level of significance was set to an alpha (α) of 0.05 and statistical power to 0.80. The standard deviation is 20 % of the maximum score of the WOMAC subscale for pain and physical function [94]. With an expected dropout rate of 20 %, the final number of participants needed is 168.

### Data analysis

Data analysis will be performed using IBM SPSS Statistics 23. The effect of group membership (aqua-cycling versus usual care) on primary and secondary outcomes will be estimated and tested for significance with a significance level set at 0.05. Furthermore, any significant changes that occur over time will be examined. Demographic variables and clinical background variables (i.e. BMI, co-morbidities) will be used as grouping variables for subgroup analysis or as covariates.

Multilevel analysis will be applied with repeated measures (level 1) that are clustered within persons (level 2), and with patients (level 1) clustered within groups (level 2). Using multilevel analysis allows the use of all data available, including dropout, loss to follow-up, missed appointments and participant incapacity.

Diary data will be examined for the time course of level of physical activity, physical functioning, knee pain and pain medication use in the intervention and control group, and for between-group differences in change. In addition, the relationship between the aqua-cycling training and the factors just referred to will be evaluated. Multilevel analysis will be used to estimate and test between-person differences and the within-person processes.

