
A 12-week group-based aqua-cycling training for mild to moderate knee OA patients was developed, because currently only a few therapeutic aqua-cycling interventions are available. The results of this study might provide guidance on the clinical use of aqua-cycling and greater insight into the effectiveness of aqua-cycling may help to broaden aquatic treatment possibilities. Furthermore, the study may support instructors of community aqua-cycling classes in dealing with participants with knee OA. For these reasons, it is important to examine whether a 12-week aqua-cycling programme, in supplement to usual care, will result in better outcomes of self-reported knee pain and physical functioning when compared with the relatively less intricate regimen usual care only.

This article provides a full description of the study’s rationale, design and method in accordance with the SPIRIT guidelines for reporting protocols of intervention trials and the CONSORT guidelines [25, 26].

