The strength of this study is the close monitoring conducted during the intervention phase with diaries, since self-reported measures might be sensitive to day-to-day variations not capturing the development of OA impairments throughout the intervention [19]. Another strong aspect of the study is the follow-up assessment 3 months after the end of the programme, something that is rarely done in aquatic exercise research [14]. Especially interesting in the follow-up assessment is the evaluation of whether participants in the intervention group continued to aqua-cycle in the community swimming pool or stayed active in another way. This will indicate if people are willing to continue aqua-cycling at their own cost or if it has helped them to become more active. The control group will be invited to attend 12 free aqua-cycling sessions in the community pool. Due to limited access to the hospital pool and the limited number of aqua bikes (n = 4), it is not possible to train both groups in the hospital. Funding restraints make it impossible to bear the costs of 24 sessions twice a week for the control group in the community pool. As the programme coordinator will give the training, there will be no difference in terms of the training content and structure. However, this waiting-list control design can influence the results of the study in two ways. On the one hand, participants in the control group might be more motivated to follow usual care instructions with regard to physical activity because they do not want to be less active than the intervention group. In addition, this group will be monitored by means of diaries too, which might also motivate them to be more active. On the other hand, it is possible that the control group participants will follow usual care recommendations less strictly as they will be waiting for their turn to try out aqua-cycling. Furthermore, the fact the control group participants did not receive any immediate and free intervention might influence motivation for further participation. Therefore, we will inform participants about group allocation before the baseline assessment. The assessments of the present study are not part of the clinical routine and participants have to come back for the assessments after giving consent and being randomised. By informing participants about group allocation prior to the baseline, we wish to prevent frustration about group allocation and possible dropout. Nevertheless, this strategy increases the risk of dropout before baseline assessment.

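### The multilevel model gives patients two level numbers and leaves 'groups' undefined, although training-group clustering can arise only in the aqua-cycling arm and the sample size states no allowance for it

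*Protocol article*

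**What the plan says.** The Data analysis section of the protocol article describes the multilevel analysis in one sentence: "with repeated measures (level 1) that are clustered within persons (level 2), and with patients (level 1) clustered within groups (level 2". It does not say what the groups are. Earlier in the same section, group membership means the trial arm.

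The Background calls the intervention "A 12-week group-based aqua-cycling training", and the Discussion refers to "the limited number of aqua bikes", giving their number as four. The section on the intervention group says that participants stay on the bike for the whole session. The section on the control group describes usual care with optional physical therapy and mentions no training groups.

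The Sample size section lists an effect, a standard deviation, a dropout rate and this: "The statistical level of significance was set to an alpha (α) of 0.05 and statistical power to 0.80". It gives no intracluster correlation (ICC), group size or design effect.

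**The concern.** One model cannot place patients at level 1 and at level 2. Outcomes are measured at baseline, 12 and 24 weeks, so a model that also carries a group level needs three levels, and the article numbers only two. The analyst must decide what a group is and where controls belong, and the standard error of the primary contrast depends on that decision.

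The design makes this more than a matter of wording. Patients who train together share a therapist, a session and each other's company, so their outcomes may be correlated. Controls have no such shared unit. If the correlation is left out of the model, the standard error is too small and the test rejects too often. If it is modelled properly, power is somewhat below what a calculation with independent patients would give.

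**Working it through.** **1. What the sentence could mean**

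- *Both clauses together, as occasions within patients within training groups.* This is a sound hierarchy once the place of controls is stated.
- *Patients within training groups, each control a group of one.* This is also about right (step 4).
- *Groups are the two arms.* Level 2 then has two units, and its variance cannot be separated from the fixed arm effect being tested.
- *Occasions within persons only.* Correlation between patients who train together is ignored (step 3).

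**2. The plan's own sample size**

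Inputs from the Sample size section: "a difference of 25 % between the aqua-cycling group and usual care group"; "The standard deviation is 20 % of the maximum score of the WOMAC subscale for pain and physical function"; alpha 0.05 (taken as two-sided; the article does not say); power 0.80; and "With an expected dropout rate of 20 %, the final number of participants needed is 168".

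Per arm, n = 2 × (1.960 + 0.842)² × (SD/difference)².

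- Difference 25, SD 20, both in percent of the scale maximum: 2 × 7.85 × 0.64 = 10.05, so 11 per arm; 22/0.8 = 27.5, so 28 in total, not 168.
- Difference as 25 % of a baseline of 39 on a 0–100 scale, or 9.75 points: 67 per arm; 134/0.8 = 167.5, so 168. A baseline of 38 also gives 168 if dropout is added as 140 × 1.2.

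The article states no such baseline, so 168 does not follow from the stated inputs. What can be used is 168 × 0.8 / 2 = 67 analysed per arm. The article's remark that about 20 participants are 30 % of the intervention group points to a similar size (20/0.30 = 66.7).

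**3. Effect of training-group clustering**

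Assumptions: stable training groups of m = 4 (from the four bikes; actual group size and stability are not stated), ICC 0.05 to 0.20 (none is given), equal total variance in the arms, one outcome time point, normal approximation.

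- Design effect in the aqua-cycling arm: DE = 1 + (m − 1) × ICC.
- Variance factor for the difference between arms: F = (DE + 1)/2.
- Type I error if the level is dropped: 2 × [1 − Φ(1.96/√F)].
- Power if the level is modelled, given 0.80 without clustering: Φ(2.802/√F − 1.96).

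| ICC | DE | F | Type I error if dropped | Power if modelled |
|---|---|---|---|---|
| 0.05 | 1.15 | 1.075 | 5.9 % | 0.77 |
| 0.10 | 1.30 | 1.15 | 6.8 % | 0.74 |
| 0.20 | 1.60 | 1.30 | 8.6 % | 0.69 |

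A simulation of 40,000 trials per ICC (17 groups of four against 68 independent controls) gave 5.8 %, 6.6 % and 8.4 % when clustering was ignored. An analysis that allowed clustering in one arm only gave about 5.0 % throughout.

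The power column depends on the starting value of 0.80. With a difference of 25 and SD 20 taken literally, power at 67 per arm stays near 1 for all three ICCs.

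**4. Controls as groups of one**

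With SD 20, the variance of the difference is 400 × DE/67 + 400/67. The standard error is √(400 × 2.15/67) = 3.58 at ICC 0.05 and √(400 × 2.30/67) = 3.71 at ICC 0.10. These equal the values from a model with the group effect in one arm only, because total variance is assumed equal in the arms.

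**The case against.** The strongest reply is that the two clauses are joined by *and*, so they may simply describe occasions within patients within groups, with careless level numbers. That reading is available, and step 4 shows that a simple patients-in-groups model can also give about the right standard error. A reader might infer that every literal reading yields a wrong standard error; the text does not support that. A reader might also infer a collapse in power because all controls would form a single cluster, but nothing in the article codes them that way.

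The article also names clustering of patients within groups, so it does not announce that this level will be dropped. That there are stable training groups of four is an inference: four bikes and continuous cycling cap a hospital session at four patients, but fixed membership is not stated. With changing membership, simple nesting would not describe the data.

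Finally, an analysis plan that is not shown may settle degrees of freedom, residual variances and the coding of controls. Their absence is no fault. What remains is what the article does state: contradictory level numbers, a group level whose meaning is open, and a sample size section with no allowance for clustering that its own analysis names.

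**Conclusion.** The point holds as an ambiguity with practical consequences. The sentence permits sound and unsound models and does not choose. Two readings are unsound: arms as level-2 units, and omission of the training-group level. The second would raise two-sided type I error to about 5.9 % at ICC 0.05, 6.8 % at 0.10 and 8.6 % at 0.20. Those figures rest on an assumed ICC and on stable groups of four.

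The cost in power is small to moderate: from 0.80 to about 0.77 at ICC 0.05 and 0.74 at ICC 0.10, if 67 analysed per arm gives 0.80 without clustering. It is tempting to put one revised power figure in the plan, or to say that 168 was computed for independent patients. Neither is supported. Because 168 does not follow from the stated inputs, the article shows only that no allowance is stated, not what the number contains.

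**What to change.** Replace the sentence with one model: occasions within patients, and patients within training groups, with the training-group random effect present only in the aqua-cycling arm. Say that controls enter as unclustered, or as groups of one. Define *training group*, and keep the trial arm as a fixed effect only.

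Derive group membership from the attendance records. The log books described under Process measures hold session dates and numbers for each patient but list no group identifier, so membership may need to be reconstructed, and doing so will show whether groups were stable.

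In the sample size section, say that no clustering allowance was stated and report the loss over an assumed ICC range, with the condition on 67 per arm made explicit. Do not put in a single new power figure while the derivation of 168 is unresolved.

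Recruitment ended in October 2015, so the number of patients will not change. The article reports data collection as ongoing until March 2016, which left time to fix the model before analysis. The cost is slightly more analysis work, possibly some work to rebuild group membership, and a slightly less favourable stated power.

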### Data monitoring

The content of the aqua-cycling intervention is comparable to existing physical activity programmes on land. Research has shown that these programmes involve no additional harm or risk to the patient [47, 95]. Aqua-cycling in rheumatic patients was evaluated in a study as safe and feasible [23]. In addition, there is adequate evidence that aquatic training and stationary cycling are beneficial and safe activities for patients with knee OA [14, 19, 20].

Because the risk of any adverse events from participation in the intervention group is small and comparable to the very low risk of adverse events from participation in land-based OA exercise programmes [47], no data monitoring committee (DMC) is needed. In case of a serious adverse event, the programme coordinator will inform all professionals involved in the study and report the event via a web portal to the accredited Medical Ethics Board within 24 h.

### Ethics

Ethical approval has been obtained from the Medical Ethics Board of MUMC^+^ (reference number 12-2-075) on 06-03-2013. The trial was registered on 21-12-2012 in the Netherlands Trial Register (NTR3766). Any modifications to the protocol that influence the execution of the trial or participant safety, i.e. changes of study design or procedures will be described in a formal amendment. All substantial amendments will require approval from the Medical Ethics Board of MUMC^+^.

Participants in the study are covered by an insurance policy that includes cover against research subject injury or death as a result of the study. The research project is covered by liability insurance which is in accordance with Section 7, subsection 6 of the Medical Research (Human Subjects) Act (WMO). A copy of the insurance certificate of MUMC^+^ is in the possession of the board of the Medical Ethics Committee.

## Discussion

This trial will demonstrate if the newly designed aqua-cycling intervention, in supplement to usual care, can help to improve impairments due to knee OA. As far as we know, the present study is the first randomised controlled trial evaluating the effects of aqua-cycling in the pre-surgical stage of OA. If this training proves to be effective, the results can provide guidance on the use of aqua-cycling in clinical and community exercise settings. Aqua-cycling could be used to increase the range of motion of the knee, lower limb muscle strength and aerobic capacity in all populations, whereas land-based training is too painful. It might also an option for patients who feel uncomfortable with traditional aquatic exercise because of poor swimming skills or hydrophobia. Previous studies have shown that aqua-cycling is well accepted by patients who have hydrophobia [22, 24]. As aqua-cycling has become a recent fitness trend in Europe and the US, many public swimming pools offer aqua-spinning to a healthy population. Exercise instructors in community exercise settings who are qualified to supervise classes with musculoskeletal disorders could use the training programme described (if proven effective) to adapt aqua-spinning classes to the needs of people with knee OA. The opportunity to participate in a modern and popular exercise class might especially be appealing to knee OA patients who want to be active and/or are young [20].

The strength of this study is the close monitoring conducted during the intervention phase with diaries, since self-reported measures might be sensitive to day-to-day variations not capturing the development of OA impairments throughout the intervention [19]. Another strong aspect of the study is the follow-up assessment 3 months after the end of the programme, something that is rarely done in aquatic exercise research [14]. Especially interesting in the follow-up assessment is the evaluation of whether participants in the intervention group continued to aqua-cycle in the community swimming pool or stayed active in another way. This will indicate if people are willing to continue aqua-cycling at their own cost or if it has helped them to become more active. The control group will be invited to attend 12 free aqua-cycling sessions in the community pool. Due to limited access to the hospital pool and the limited number of aqua bikes (n = 4), it is not possible to train both groups in the hospital. Funding restraints make it impossible to bear the costs of 24 sessions twice a week for the control group in the community pool. As the programme coordinator will give the training, there will be no difference in terms of the training content and structure. However, this waiting-list control design can influence the results of the study in two ways. On the one hand, participants in the control group might be more motivated to follow usual care instructions with regard to physical activity because they do not want to be less active than the intervention group. In addition, this group will be monitored by means of diaries too, which might also motivate them to be more active. On the other hand, it is possible that the control group participants will follow usual care recommendations less strictly as they will be waiting for their turn to try out aqua-cycling. Furthermore, the fact the control group participants did not receive any immediate and free intervention might influence motivation for further participation. Therefore, we will inform participants about group allocation before the baseline assessment. The assessments of the present study are not part of the clinical routine and participants have to come back for the assessments after giving consent and being randomised. By informing participants about group allocation prior to the baseline, we wish to prevent frustration about group allocation and possible dropout. Nevertheless, this strategy increases the risk of dropout before baseline assessment.

In conclusion, this trial will increase the knowledge of aqua-cycling and might be a useful addition to aquatic exercise training. As with aquatic treadmill training, it is possible to adequately monitor and modify exercise intensity since pedalling rate and resistance can be adjusted [96]. In addition, the exercise programme is based on exercise guidelines and the exercise intensity will be measured by pedalling frequency and resistance, average heart rate, peak heart rate and perceived exertion during the different parts of the conditioning phase. Recent reviews strongly recommend using and reporting exercise intensity, as will be done in this study, in order to obtain a better understanding of the dose-response relationship in aquatic exercise [14, 15].

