#### Exclusion criteria

Potential participants with any contra-indication for aquatic exercise therapy such as [1] severe, unstable cardiorespiratory co-morbidities and [2] open wounds, or patients on a [3] waiting list for total knee surgery were excluded from participation in this study. Furthermore, all potential participants who met one of the following criteria were excluded given that these conditions could limit safe and full participation in the study or impede the perception of symptoms of knee OA: [4] corticosteroid injection <3 months and/or hyaluronic acid injection <6 months, [5] severe joint complaints (other than knee joint) that interfere the ability to participate in an exercise programme, [6] symptomatic and radiological apparent hip OA, [7] inflammatory joint diseases, [8] inability to safely enter and exit the pool and [9] fear of water.

Eligible patients first received verbal information by telephone. Interested patients were contacted by the programme coordinator after their consultation visit at the MUMC^+^. If their interest in participation continued after the telephone call, the programme coordinator sent additional information by mail. Each potential participant could consider participation for 1 week and was instructed to hold off any physical therapy until the randomisation results were known. If a candidate decided to participate, they had to sign an informed consent form in which they declared their voluntary participation. The programme coordinator checked incoming applications, including two short questionnaires, to screen for any contra-indications for physical activity using the physical activity readiness questionnaire (PAR-Q) and to screen for anxiety and depression using the HADS [28, 29]. In case of any doubts about a patient’s mental and/or physical health, the patient concerned was advised to contact a medical specialist for examination or advice.

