After providing their informed consent, participants were randomly assigned to either the usual care control group or a 12-week aqua-cycling programme at MUMC^+^. Having completed the baseline assessment, participants in the intervention group started the aqua-cycling programme (24 sessions) and the control group could start with physical therapy and continue other usual care routines. The post-programme and follow-up measurements were scheduled after 12 and 24 weeks. After the last assessment, the control group is offered 12 sessions of aqua-cycling in a public swimming pool. The intervention group can also join this group after the 12-week intervention phase, but will have to pay the regular rate for aquatic fitness charged by the community pool. An overview of the participant timeline is given below in Fig. 1.

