### Outcome measures

The current study investigates the effect of aqua-cycling on impairments due to knee OA, such as knee pain, reduced physical functioning over the previous week and on the assessment day, and knee stiffness. It also seeks to make an overall assessment of disease severity and lower limb muscle strength compared with a control group receiving usual care.

Furthermore, the phenomenon of aqua-cycling is explored in a more general health context through evaluating the effect of aqua-cycling on functional capacity, physical activity level and quality of life. Psychological measures on self-efficacy and fear of movement are also assessed. Outcomes are assessed in person, but to keep the number of missing values as small as possible, all questionnaires will be sent by mail to any participants unable to come to the MUMC^+^. An overview of all measures and timing of assessment is given in Table 2.

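### The baseline KOOS is taken after participants learn their arm, so reporting can shift it by arm, and those who leave before it are outside the planned model

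*Protocol article*

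**What the plan says.** The order of events is clear from two places in the protocol article. The end of the Exclusion criteria section says: "After providing their informed consent, participants were randomly assigned to either the usual care control group or a 12-week aqua-cycling programme". Treatment starts only once baseline has been completed. The Discussion explains that the assessments lie outside routine care and that "participants have to come back for the assessments after giving consent and being randomised". It then states: "Therefore, we will inform participants about group allocation before the baseline assessment". The purpose is to limit frustration about allocation and later dropout. The authors concede the price: "Nevertheless, this strategy increases the risk of dropout before baseline assessment".

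The primary outcome is KOOS pain and physical functioning, which the participant completes in about 10 minutes (Primary outcome). Participant blinding is ruled out (Study design). Before randomisation, applicants already return forms: "The programme coordinator checked incoming applications, including two short questionnaires", namely the PAR-Q and the HADS (Exclusion criteria). No KOOS is described at that stage.

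On incomplete data, the Data analysis section says: "Using multilevel analysis allows the use of all data available, including dropout, loss to follow-up". The Outcome measures section adds a postal route: "all questionnaires will be sent by mail to any participants unable to come".

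**The concern.** There are two separate problems.

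**Reporting at baseline.** A self-reported score can respond to hope or disappointment. The Discussion itself expects frustration over allocation and says that controls may lose motivation because they receive nothing immediate and free. The KOOS baseline is collected after that reaction has had its chance. Blinded assessors do not protect a form that the participant fills in. If the arms report differently at baseline for this reason, any analysis that uses baseline as a reference or covariate carries some of the difference into the treatment effect.

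**Loss before the first record.** A multilevel model uses every outcome record it is given. A person who leaves on learning their arm, before the first KOOS, has none. The Data analysis section relies on the model for dropout, yet the one kind of dropout that the Discussion says the design makes more likely lies outside it. That loss may plausibly differ by arm. The 20 % dropout allowance in the Sample size section protects power, not comparability. The postal questionnaires serve people who cannot attend, not people who have left.

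**Working it through.** The protocol gives no figure for either effect, so there is none to reproduce. The numbers below show scale only.

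**Inputs from the protocol (Sample size, Study design)**
- N = 168, 20 % dropout, 1:1 allocation: 168 × 0.8 = 134.4, about 67 completers per arm.
- SD = 20 % of the maximum WOMAC subscale score, taken here as 20 points on a 0-100 scale.
- α = 0.05. Sidedness is not stated; two-sided is assumed.

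**Assumed inputs**
- A between-arm reporting shift s of 2-5 points at baseline.
- Baseline to 12-week correlation r = 0.5 (0.3 to 0.7 as a check).
- Equal SDs at both times and no true treatment effect.

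Bias is not expressed as a share of the target difference, because the protocol does not say to what the hypothesised 25 % applies.

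**Step 1. Standard errors**
- Change score: 20 × √(2(1 − r)) × √(2/67) = 20 × 1 × 0.1728 = 3.46.
- Baseline-adjusted: 20 × √(1 − r²) × √(2/67) = 17.32 × 0.1728 = 2.99.

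**Step 2. Bias and type I error if the shift has gone by 12 weeks**

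The absolute bias b is s for a change score and r·s with adjustment. The rejection probability is Φ(b/SE − 1.96) + Φ(−b/SE − 1.96).

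| Shift s | Change: bias | Change: type I error | Adjusted: bias | Adjusted: type I error |
|---|---|---|---|---|
| 2 | 2.0 | 0.089 | 1.0 | 0.063 |
| 3 | 3.0 | 0.140 | 1.5 | 0.079 |
| 5 | 5.0 | 0.304 | 2.5 | 0.133 |

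With r between 0.3 and 0.7 the ranges over these shifts widen to 0.08-0.46 (change) and 0.05-0.29 (adjusted).

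**Step 3. What if the shift persists?**

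Let a fraction p of the shift remain at 12 weeks. The bias is (p − 1)s for change, (p − r)s with adjustment, and p·s for a follow-up comparison that ignores baseline. For s = 5 and r = 0.5, in absolute value:

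| p | Change | Adjusted | Follow-up only |
|---|---|---|---|
| 0 | 5.0 | 2.5 | 0 |
| 0.5 | 2.5 | 0 | 2.5 |
| 1 | 0 | 2.5 | 5.0 |

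The change-score bias shrinks as the shift persists. No single contrast is best for every p.

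**Step 4. Loss before baseline**

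If a fraction q of controls leaves and would have differed from those who stay by D points, the mean of the remaining controls is off by q × D. With q = 0.10 and D = 5 that is 0.5 points; with q = 0.20 and D = 10 it is 2 points. Both inputs are assumed.

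**The case against.** Five counter-arguments deserve weight.

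- **The model is not fully specified.** For the primary outcome the Data analysis section promises a multilevel repeated-measures estimate of the group effect. It speaks of between-group differences in change only for the diary data. A reader might infer that change from baseline is the stated primary contrast, and hence that the 9-30 % range is the trial's type I error. The document does not say that. How baseline enters is ordinary SAP content, and with adjustment the illustrative range is about 6-13 %. This stands.
- **The shift may persist.** Participants stay unblinded, so their reporting at 12 weeks may also depend on arm. Step 3 shows that the change-score bias is then smaller, and that a comparison ignoring baseline can be the worse choice. A reader might conclude that the primary analysis must be replaced; the documents do not support that. An earlier baseline would not remove reporting bias at follow-up either.
- **Early leavers lack follow-up under either order.** A reader might infer that moving the KOOS would restore intention-to-treat. It would give these people a baseline record but no 12-week outcome. What survives is narrower: the reliance on the model for dropout does not reach them.
- **The dropout risk is disclosed.** It is, and a reason is given. Biased baseline reporting is not mentioned, and no handling is stated for either problem.
- **Recruitment is over.** The Setting and participants section dates its end to October 2015, so the baseline can no longer be moved. Analysis and reporting can still be settled, since Trial status has data collection running to March 2016.

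**Conclusion.** The concern holds in limited form. The baseline of the self-reported primary outcome is a post-disclosure measurement in an unblinded trial, and participants lost between disclosure and baseline contribute no KOOS to the model on which the protocol relies for dropout. Both follow from the text.

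The size and direction of any bias cannot be learned from it. The illustrative figures (2-5 points with about 9-30 % type I error for a change score; 1-2.5 points with about 6-13 % after adjustment) rest on an assumed shift that has vanished by 12 weeks, SD 20, 67 per arm and r = 0.5. They do not show that the trial is biased by these amounts or that the planned analysis is invalid.

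The order was avoidable at little cost. A short self-completed form could have gone with those already returned before randomisation, without giving up early disclosure.

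**What to change.** **Design (this trial had it been open, or a successor).** Collect the KOOS and the other self-report baselines in the application pack with the PAR-Q and HADS, before allocation is disclosed. Leave the hospital performance and strength tests where they are. Cost: a slightly longer pack.

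**Participants already enrolled**
1. Keep the planned multilevel analysis as primary.
2. Prespecify a sensitivity analysis of 12-week KOOS by arm that does not use the post-disclosure baseline and adjusts only for pre-randomisation variables: eligibility pain rating, HADS and Kellgren/Lawrence grade. Eligibility restricts these to narrow ranges (pain 4-7, HADS below 8, grade 1-3), so expect little gain from them. At r = 0.5 the standard error rises from 2.99 to as much as 3.46, a variance ratio of 1/(1 − 0.25) = 1.33, equivalent to up to 33 % more patients. That is acceptable for a sensitivity analysis.
3. Report by arm how many were randomised but lost before baseline, keep all randomised participants in the denominator, and add a missing-not-at-random sensitivity analysis. Screening variables alone cannot correct a loss driven by reaction to allocation.
4. Reword the Data analysis section to say that the multilevel model does not cover participants lost before their first KOOS.

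Items 2 to 4 cost analysis time and wording; no new data are needed.
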